### Outcome measures

Table 1 summarises the outcome measures that are being collected to determine treatment efficacy. Our primary outcomes are recommended validated measures of pain and physical function for knee OA [31]. These will be measured at baseline, 3 months and 6 months. Conclusions regarding treatment efficacy will be based on the changes in primary outcome measures from baseline to 6 months. Our two primary outcomes are:

**Table 1 T1:** Summary of primary and secondary outcome measures collected to determine treatment effectiveness

**Outcome**	**Measurement tool**
**Primary**	
Knee pain on walking	11-point numerical rating scale
Physical function	WOMAC physical function subscale
**Secondary**	
Global rating of change in:	7-point scales
i) Knee pain	
ii) Physical function	
Knee pain	WOMAC pain subscale
Knee pain	ICOAP
Knee stiffness	WOMAC stiffness subscale
Health-related quality of life	AQoL-6D
Physical activity	PASE

WOMAC = Western Ontario and McMaster Universities Osteoarthritis Index; PASE = physical activity scale for the elderly; ICOAP = Intermittent and Constant Osteoarthritis Pain questionnaire; AQoL-6D = Assessment of Quality of Life instrument (version 6D).

#### Knee pain on walking measured by an 11-point NRS

Overall average pain on walking over the past week will be self-reported via a NRS with terminal descriptors of ‘no pain’ (score 0) and ‘worst pain possible’ (score 10). Such measurement has demonstrated reliability in OA [32].

#### Physical function measured by the function subscale of the WOMAC

Difficulty with physical functioning will be measured by the Western Ontario and McMaster Universities (WOMAC) Osteoarthritis Index (Likert version 3.1) [33]. This is a disease-specific self-report instrument whose validity, reliability and responsiveness have been demonstrated in an extensive range of OA studies [34]. The physical function subscale contains 17 questions (each answered on a Likert scale where 0 = no dysfunction and 4 = extreme dysfunction) and has a total score ranging from 0 (no dysfunction) to 68 (maximum dysfunction).

Our secondary outcome measures, which will be administered at baseline and at 6 months (with the exception of some outcomes as detailed below), include:

#### Participant-perceived response to treatment measured on 7-point scales

Participants will rate their overall global change in a) pain and b) physical function since enrolling in the study, at 3 months and 6 months. The terminal descriptors on the 7-point scales will be ‘much worse’ to ‘much better’ [35]. Participants who report ‘moderately better’ or ‘much better’ will be classified as improved.

#### Knee pain measured by the WOMAC pain subscale

This subscale contains 8 questions (each answered on a Likert scale where 0 = no pain and 4 = extreme pain) and has a total score ranging from 0 (no pain) to 20 (maximum pain). In addition to baseline and 6 months, this will also be administered at 3 months.

#### Knee stiffness measured by the WOMAC stiffness subscale

This subscale contains 2 questions (each answered on a Likert scale where 0 = no stiffness and 4 = extreme stiffness) and has a total score ranging from 0 (no stiffness) to 8 (maximum stiffness). In addition to baseline and 6 months, this will also be administered at 3 months.

#### Knee pain measured by the ICOAP

The Intermittent and Constant Osteoarthritis Pain (ICOAP) questionnaire [36] will also be used to assess knee pain. The ICOAP contains 11 questions, each scored from 0–4, giving a range of possible scores from 0 (no pain) to 44 (maximum pain).

#### Health-related quality of life measured by the AQoL-6D

The Assessment of Quality of Life (AQoL) instrument [37] (version AQoL-6D) contains 20 items assessing independent living, mental health, relationships, pain, coping and senses. Scores range from -0.04 to 1.00 and higher scores indicate better quality of life.

#### Physical activity levels measured by the PASE

The Physical Activity Scale for the Elderly (PASE) measures physical activity over the previous week [38]. Scores range from 0 to over 400, with higher scores indicating greater physical activity.

### Additional measures

A range of additional measures will be collected for the purposes of answering related questions about biomechanical effects of the unloading and control shoes, and for subsequent analyses of potential mediating effects on clinical outcomes. These measures will not be used, however, to determine treatment efficacy. Additional measures that will be obtained include radiographic measures of knee alignment; the painDETECT questionnaire for identifying neuropathic pain [39]; a rating of participant expectation of treatment outcome measured on a 5-point ordinal scale; objective measures of foot posture, mobility and anthropometry including the Foot Posture Index [40]; and lower limb kinetics and kinematics during walking measured with three-dimensional gait analysis (Vicon, Oxford, UK; AMTI, Massachusetts, USA) and; in-shoe regional foot pressure patterns (Novel Pedar, Munich, Germany).

### Sample size calculations

The trial is powered to detect clinically important changes in the primary outcomes of knee pain on walking (NRS) and change in physical function (WOMAC). The minimum clinically important difference to be detected in OA trials is a change in pain of 1.8 units (out of 10) [41] and change in function of six units (out of 68) [42]. Our calculations are based on SD’s from our unpublished pilot data of the effects of unloading shoes, and on control group data from our previous RCT of lateral wedged insoles [43]. We assume a between-subject SD of 2.5 for pain and 10.5 units for WOMAC physical function, and a baseline to 12-month correlation in scores of 0.29 for pain and 0.51 for physical function. These assumptions, together with an analysis of covariance adjusted for baseline scores, require a sample size of 41 participants per group to achieve 90% power to detect the minimum clinically important difference in pain. A similar analysis for function scores requires 65 participants per group. Allowing for a 20% attrition rate, we will recruit 82 participants per arm, or 164 participants in total.

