## Methods/design

### Trial design

The SHARK (SHoes for ARthritis of the Knee) trial is a two-arm participant- and assessor-blinded parallel-group RCT comparing unloading shoes to control (non-unloading) shoes (Figure 1). The protocol conforms to CONSORT guidelines for reporting of non-pharmacological interventions [27]. The primary end-point for analysis of outcomes is after 6 months of treatment.

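### The 41 (pain) and 65 (function) per group match an unadjusted comparison, not the stated baseline-adjusted ANCOVA; the slip is conservative, but the basis and power given for 164 are wrong

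*Protocol article*

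**What the plan says.** The Sample size calculations section sets targets of 1.8 points on the 0–10 pain scale and 6 points on the 0–68 WOMAC function scale. On variability it says "We assume a between-subject SD of 2.5 for pain and 10.5 units for WOMAC physical function", and it adds "a baseline to 12-month correlation in scores of 0.29 for pain and 0.51 for physical function". It then names the method and the result: "These assumptions, together with an analysis of covariance adjusted for baseline scores", are said to "require a sample size of 41 participants per group to achieve 90% power to detect the minimum clinically important difference in pain". For function it says "A similar analysis for function scores requires 65 participants per group". Allowing for 20% attrition, it arrives at 82 per arm and 164 in total.

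Two other places matter. The Statistical analyses section plans a comparison of change adjusted for the baseline value of the outcome, with significance at p below 0.05. The Trial design section fixes the time-point: "The primary end-point for analysis of outcomes is after 6 months of treatment".

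**The concern.** The text presents 41 and 65 as the output of a calculation that uses the correlations. Baseline adjustment reduces the outcome variance by the factor 1 − r², so a correlation of 0.51 should cut the function sample size by about a quarter. The printed figures show no such reduction.

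Function is the outcome that matters here, because its 65 per group sets the enrolment of 164. If 65 is not the ANCOVA figure, the reason given for the trial's size is wrong, and 90% is not the power of the baseline-adjusted analysis that will be run. A reader who checks the calculation, or reuses it to plan another trial, would be misled about what the assumptions imply.

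A smaller point belongs with this one. The correlations run from baseline to 12 months, whereas the primary time-point is 6 months, and the section does not say that the one stands in for the other.

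**Working it through.** **Inputs** (Sample size calculations, except alpha):
- Differences d: 1.8 (pain), 6 (function)
- SDs: 2.5, 10.5
- Correlations r: 0.29, 0.51
- Power 90%, attrition 20%, equal arms
- Alpha 0.05 (Statistical analyses); two-sided is my assumption

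**Step 1: reproduce the printed figures.** For an unadjusted two-sample comparison, n per group = 2(1.960 + 1.2816)² SD²/d², where (1.960 + 1.2816)² = 10.507.
- Pain: 2 × 10.507 × 6.25/3.24 = 40.5, rounded up to 41
- Function: 2 × 10.507 × 110.25/36 = 64.4, rounded up to 65

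Both match exactly, and the correlations are not used.

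**Step 2: apply the stated method.** ANCOVA multiplies each by 1 − r².
- Pain: 1 − 0.29² = 0.9159; 40.54 × 0.9159 = 37.1, rounded up to 38 (39 by noncentral t)
- Function: 1 − 0.51² = 0.7399; 64.36 × 0.7399 = 47.6, rounded up to 48 (49 by noncentral t)

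**Step 3: try another reading.** An unadjusted analysis of change scores has variance factor 2(1 − r).
- Pain: 40.54 × 1.42 = 57.6, rounded up to 58
- Function: 64.36 × 0.98 = 63.1, rounded up to 64

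This comes close for function but is far off for pain, so it does not explain the pair. One-sided 0.05 at 90% power gives ANCOVA sizes of 31 and 39, which are further away.

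**Step 4: attrition.**
- As printed: 65/0.8 = 81.25, so 82 per arm and 164 in total. This step is correct.
- ANCOVA function figure: 48/0.8 = 60 per arm, 120 in total. With the t-based 49, 49/0.8 = 61.25, so 62 per arm and 124 in total.

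**Step 5: power at 65 completers per arm,** two-sided 0.05, using SD√(1 − r²). No 6-month correlation is given, so function is shown over a range of r. Percentages are by noncentral t.

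| Outcome | r | Power |
|---|---|---|
| Function | 0 | 90% |
| Function | 0.3 | 92% |
| Function | 0.4 | 94% |
| Function | 0.51 | 96% |
| Pain | 0 | 98% |
| Pain | 0.29 | 99% |

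At 41 per group, ANCOVA power for pain with r = 0.29 is about 92%.

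**The case against.** The strongest defence is that nothing is lost. With 65 completers per arm, power for function is about 90% even if the baseline score carries no information, and higher if it does, so the target is met either way. The attrition step is right, so 164 is a correct consequence of 65. For pain the gap is only two or three participants per group, and pain does not set the total. All of this stands, and it limits the point to a conservative misstatement carried mainly by the function figure.

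It could also be said that the SDs were already residual SDs, or that adjustment was deliberately held back as a margin. The text supports neither. It calls the SDs between-subject, lists the correlations among the assumptions, and attributes the sizes to the ANCOVA.

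On the time-point, the defence is largely right. The section openly labels the correlation as a 12-month one and says its inputs come from pilot data and an earlier trial's control group. Borrowing an external value is ordinary planning practice. If the correlation did not enter 41 and 65, its time-point cannot have distorted them. It matters only once an adjusted power is quoted.

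A reader might also infer that the correlations were certainly left out of the calculation. The exact match makes that likely, but the working is not shown. What can be said is that the figures do not reproduce under the stated method and do reproduce under an unadjusted one.

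**Conclusion.** The point holds as a conservative error in the stated basis of the sample size. Under the section's own inputs, the function size by the stated ANCOVA is about 48 to 49 per group rather than 65, and the total about 120 to 124 rather than 164. The pain size is 38 to 39 rather than 41, which alone would hardly merit comment. The stated 90% understates power for the baseline-adjusted analysis by an amount that depends on a 6-month correlation the document does not give. This rests on a two-sided 0.05 test and on reading the SDs as unadjusted, as the text describes them.

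Three stronger readings are not supported:
- **That the trial is underpowered or 164 is miscalculated.** The error runs the other way, and 164 follows from 65 and 20% attrition.
- **That a null result must be read differently.** What a null result rules out is read from the observed confidence interval, not from a planning-stage detectable difference, and rewording this section leaves the interval unchanged.
- **That the spare power should be assigned to multiplicity control over the two primary outcomes.** That is a separate design choice and does not follow from this discrepancy.

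**What to change.** Correct the wording of Sample size calculations and keep 164.

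1. Either state that 41 and 65 per group are sizes for an unadjusted two-sample comparison, deliberately conservative, with baseline adjustment held in reserve; or give the ANCOVA sizes (about 38 for pain and 48 for function, or 39 and 49 by the t-based calculation) and explain why 82 per arm is kept. State that the test is two-sided, if it is.
2. Give power at 65 completers per arm as a range over the correlation, not as one figure: for function about 90% at r = 0, 92% at 0.3, 94% at 0.4 and 96% at 0.51; for pain about 98% to 99%.
3. Label the baseline-to-12-month correlations as stand-ins for the 6-month endpoint, or replace them with 6-month values if the sponsor has them.

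The cost is a few sentences. Enrolment, conduct and the planned analysis are unchanged.

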### Statistical analyses

Our biostatistician will analyse data in a blinded manner, with p values less than 0.05 considered significant. Main comparative analyses between groups will be performed using intention-to-treat. This analysis will include all participants including those who have missing data and those who do not fully adhere to the protocol. To account for missing data, multiple imputation of missing follow-up measures, assuming data are missing at random and follow a multivariate normal distribution, will be performed as a sensitivity analysis.

Demographic characteristics, as well as baseline scores on primary and secondary outcome measures, will be presented to assess baseline comparability of treatment groups. These variables will also be examined for those participants who withdraw from the study and those who remain.

Descriptive statistics will be presented for each group as the mean change (standard deviation, 95% confidence intervals) in the outcomes from baseline to each time-point. For continuous outcome measures, differences in mean change (baseline minus follow-up score) will be compared between groups using linear regression random effects modelling adjusted for baseline values of the outcome. Model diagnostic checks will utilise residual plots. Similar regression models for binary and ordinal outcome measures will use random effects logistic and proportional odds models, respectively. We will also perform a per protocol analysis as appropriate.

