Clinical guidelines emphasise that appropriate footwear should be worn by people with knee OA [17]. This recommendation is based on expert opinion given the scant research evidence available. Wearing shoes significantly *increases* medial knee load compared to barefoot walking [18,19]. Recent research, by ourselves and others, has developed specialised shoes for people with knee OA with variable-stiffness soles that are denser laterally compared to medially in order to reduce the KAM [20-22]. Thus, when weightbearing, the greater medial compressibility effectively creates a laterally angled shoe that reduces the frontal plane lever arm of the ground reaction force at the knee joint centre, reducing the KAM [23,24]. These types of modified shoes can immediately reduce the KAM by 3.5-7.9% in people with medial knee OA [20,25]. In a single case study involving a patient with an instrumented knee replacement, variable-stiffness shoes reduced the peak KAM by 13.3% and medial joint contact force by 12.3% [22]. Furthermore, change in KAM correlated with change in contact force, validating the load-modifying effects of unloading shoes for knee OA.

Relative to their biomechanical effects, there is very little known about whether unloading shoes can reduce the pain and physical dysfunction associated with knee OA. There is only one randomized controlled trial (RCT) evaluating clinical benefits of variable-stiffness unloading shoes for knee OA [25,26]. The unloading shoes resulted in significant within-group pain reductions after 6 and 12 months of use, however the change in symptoms was not significantly different to that seen in the group wearing control shoes. This may be because of the relatively small sample size utilized (n = 79) and/or the large drop-out rate in the control group (n = 13 out of 39, 33%) by 6 months. Further RCTs are required before the efficacy of unloading shoes for managing the symptoms of OA can be known.

The primary aim of this study is to evaluate the efficacy of specialized unloading shoes on OA-associated symptoms in people with knee OA. We hypothesise that unloading shoes will reduce pain and improve self-reported physical function after 6 months when compared to control shoes.

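### The one missing-data sensitivity analysis named keeps the missing-at-random assumption of the main analysis, so agreement between them says little about outcome-related dropout

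*Protocol article*

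**What the plan says.** All of this is in the protocol article.

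- **Main analysis** (Statistical analyses). Changes in continuous outcomes "will be compared between groups using linear regression random effects modelling adjusted for baseline values of the outcome". On the analysis set: "This analysis will include all participants including those who have missing data and those who do not fully adhere to the protocol".
- **Sensitivity analysis** (same section). Missing follow-up measures are multiply imputed, "assuming data are missing at random and follow a multivariate normal distribution, will be performed as a sensitivity analysis". No other missing-data sensitivity analysis is named.
- **Related analyses** (same section). On baseline characteristics and scores: "These variables will also be examined for those participants who withdraw from the study and those who remain". On adherence: "We will also perform a per protocol analysis as appropriate".
- **Expected loss** (Sample size calculations). "Allowing for a 20% attrition rate, we will recruit 82 participants per arm, or 164 participants in total".
- **Earlier experience** (Background). The only previous randomised trial of such shoes found no between-group difference. The article offers two possible reasons, a small sample and "the large drop-out rate in the control group (n = 13 out of 39, 33%) by 6 months".

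**The concern.** A sensitivity analysis for missing data is useful when it changes the assumption that the data cannot verify. Here that assumption is that, given what was observed, dropouts would have scored like those who stayed. A random-effects model fitted by likelihood to incomplete data makes this assumption, and the named imputation makes it explicitly. If dropouts in one arm do worse or better than their observed data predict, both analyses tend to be wrong in the same direction by a similar amount.

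The related analyses do not close the gap. Comparing baseline variables of withdrawals and remainers is descriptive and cannot see dependence on the unobserved 6-month score. The per protocol analysis concerns adherence.

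The issue is relevant here because the article budgets for 20% loss and itself points to heavy, one-sided loss in the earlier trial. Both primary outcomes are self-reported, and discomfort or lack of benefit are plausible reasons to leave. What is at stake is whether a modest positive or null result can be defended against the objection that dropout produced it.

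**Working it through.** **Inputs.** From Sample size calculations: targets of 1.8 (pain) and 6 (WOMAC function); SD 2.5 and 10.5; correlation with baseline 0.29 and 0.51; 90% power; 20% attrition; 82 per arm. From Statistical analyses: significance level 0.05, taken as two-sided because the side is not stated. From Background: 13/39 = 33% control dropout in the earlier trial. The size of any departure from missing at random (delta) is **assumed**: half the target to the full target, 0.9 to 1.8 for pain and 3 to 6 for function.

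**1. The plan's own figures.** With n = 2(1.96 + 1.2816)² SD²/d² per group:
- pain: 2 × 10.51 × 6.25/3.24 = 40.5, so 41;
- function: 2 × 10.51 × 110.25/36 = 64.4, so 65;
- attrition: 65/0.8 = 81.25, so 82 per arm and 164 in total.

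The figures 41 and 65 reproduce without the baseline adjustment that the article says was applied (with it: 38 and 48). That is a separate matter and does not affect this point.

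**2. Smallest significant difference.** Completers per arm: 82 × 0.8 = 65.6. SE = SD × √(1 − r²) × √(2/65.6).
- Pain: 2.5 × 0.957 × 0.1746 = 0.418; × 1.96 = 0.82.
- Function: 10.5 × 0.860 × 0.1746 = 1.577; × 1.96 = 3.09.

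**3. Effect of a departure.** Let D be the benefit of unloading shoes (positive is better), p the fraction missing, and delta how much worse dropouts are than predicted. Then

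D(true) = D(missing at random) + p_control × delta_control − p_unloading × delta_unloading.

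| Scenario | Pain (delta 0.9 / 1.8) | Function (delta 3 / 6) |
|---|---|---|
| Unloading arm only, 20% missing | −0.18 / −0.36 | −0.6 / −1.2 |
| Both arms, 20% missing in each | 0 / 0 | 0 / 0 |
| Both arms, 33% control and 20% unloading (assumed pairing) | +0.12 / +0.23 | +0.39 / +0.78 |

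As a share of the pain target, the first row is 0.18/1.8 = 10% to 0.36/1.8 = 20%. In the last row the true benefit exceeds the missing-at-random estimate, so the bias runs against the unloading shoes.

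**4. Tipping points**, unloading arm only, 20% missing, SE held at its completer value: delta = (observed difference − smallest significant difference)/0.20.
- Observed pain difference 1.8: (1.8 − 0.819)/0.20 = 4.9 points (2.0 SD).
- Observed function difference 6: (6 − 3.09)/0.20 = 14.5 units (1.4 SD).
- Observed pain difference 1.0: (1.0 − 0.819)/0.20 = 0.9 points.

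A delta of 0.9 removes significance from observed pain differences up to 0.82 + 0.18 = 1.00, and a delta of 1.8 from those up to 0.82 + 0.36 = 1.18.

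**5. Do the two analyses move together?** Simulation of the pain outcome: 82 per arm, no true effect, one follow-up score, 2,000 runs. Dropout was about 20% in each arm, random in the control arm. In the unloading arm it was likelier with worse 6-month pain (assumed odds ratio about 1.8 per point).
- Mean bias: −0.53 points for the baseline-adjusted regression on observed data and −0.53 for missing-at-random imputation (negative favours unloading shoes).
- Type I error: 25% and 26%.
- Correlation between the two estimates: 0.99.

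This illustrates the mechanism and does not forecast the trial. The dropout mechanism is invented, and there is no 3-month score or auxiliary variable in the imputation.

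**The case against.** **It is a condensed article, and a fuller analysis plan may add more.** That stands as a limit: the statement covers only what the article names. It does not dispose of the point, because the article is not silent. It states the method, its assumption and its role.

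**The main model's assumption is never stated.** True. It is inferred from a random-effects model that retains participants with missing data, assuming likelihood estimation.

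**Imputation can do more than the main model.** This stands in part. The trial collects 3-month primary outcomes, monthly comfort ratings, and adherence and co-intervention records. Imputing from these could make missing at random more believable and bring in participants with no follow-up score. A reader might infer that the imputation is worthless or can show nothing, and the documents do not support that. But the article names no imputation variables, and the analysis would remain a missing-at-random one. The simulated 0.99 correlation follows largely from imputing on the same variables that the main model uses.

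**The size is modest.** Agreed for effects near the target. A reader might also take the 33% control dropout as showing that this trial would overstate benefit. It does not: pairing 33% with 20% is an assumption, and with worse outcomes among dropouts in both arms the bias goes against the unloading shoes.

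**Stopping shoe wear is not missing data.** Correct. Those who stop wearing the shoes but return questionnaires stay in the intention-to-treat analysis. Only missing scores matter here.

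**Conclusion.** The point holds in a limited form. The named sensitivity analysis does not vary the assumption most at risk, so its agreement with the main analysis would be weak evidence of robustness to outcome-related dropout.

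At 20% attrition, a one-arm departure of 0.9 to 1.8 points shifts the pain difference by 0.18 to 0.36. This leaves a result near 1.8 standing but could remove significance from one near the threshold (about 0.8 to 1.0, and up to 1.18 at the largest delta). Equal departures with equal dropout cause no bias.

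This rests on assumed deltas, the article's SDs and correlations, a two-sided 5% level and likelihood fitting of the main model. The documents do not support saying that robustness goes wholly untested, that agreement will be reported as robustness, or that no analysis plan addresses the matter.

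**What to change.** 1. Keep the missing-at-random imputation as a supporting analysis, and state which auxiliary variables it uses (for example 3-month scores, comfort, adherence).
2. Add, for pain and WOMAC function at 6 months, a delta-adjusted (pattern-mixture) imputation. Shift the imputed scores by a range fixed before unblinding, for example 0 to 1.8 pain points and 0 to 6 WOMAC units, in the unloading arm alone, the control arm alone and both.
3. Extend the range as far as needed to report the tipping point. For an observed difference at the target, it lies well beyond 1.8 or 6.
4. If the 7-point global ratings are imputed, use an ordinal or predictive-mean-matching method in place of the multivariate normal, which suits a short ordered scale poorly.

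Cost: a short paragraph and a few lines of code, with no new data. The downside is that a borderline result may have to be reported as less robust.

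### The one stated covariate, the baseline outcome, does not exist for the global ratings of change, and the K-L randomisation stratum is not among the stated adjustments (minor)

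*Protocol article*

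**What the plan says.** The Statistical analyses section of the protocol article gives one model sentence for continuous outcomes: "differences in mean change (baseline minus follow-up score) will be compared between groups using linear regression random effects modelling", with the baseline value of the outcome as the stated adjustment. The next model sentence extends this: "Similar regression models for binary and ordinal outcome measures will use random effects logistic and proportional odds models, respectively". No random effect is named, and no other covariate.

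Three other parts of the article bear on this:

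- **Randomisation.** The Randomisation and allocation concealment section uses permuted blocks of 6 to 12, stratified by K-L grade (2, 3 or 4). Baseline outcome measures are taken before randomisation.
- **Global ratings.** Participants rate their "overall global change in a) pain and b) physical function since enrolling in the study, at 3 months and 6 months". The moderately and much better categories count as improved.
- **Visit schedule.** Secondary outcomes default to baseline and 6 months. The global ratings, WOMAC pain and WOMAC stiffness also have a 3-month value. ICOAP, AQoL-6D and PASE do not.

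The Trial design section places the primary end-point at 6 months, and the Outcome measures section adds: "Conclusions regarding treatment efficacy will be based on the changes in primary outcome measures from baseline to 6 months".

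**The concern.** One adjustment rule is written for all outcomes, but it does not suit all of them. A rating of change since enrolment cannot have a baseline score, so a model adjusted for the baseline outcome has nothing to adjust for. The analyst must then either leave these models unadjusted or choose a covariate later.

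The randomisation is balanced within K-L grade, but K-L grade is not in the stated model. If severity predicts outcome, a model without it leaves the between-grade variation in the residual. Standard errors are then larger than the design warrants.

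The random-effects wording covers every continuous outcome, including three with a single follow-up, where a participant effect has nothing to be estimated from.

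What is at stake is some precision, and a covariate choice that should be settled before the blind is broken.

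**Working it through.** **1. Which outcomes can the stated rule serve?**

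| Outcome | Baseline value | Follow-ups | Baseline adjustment possible | Participant effect separable |
|---|---|---|---|---|
| NRS pain, WOMAC function | yes | 3, 6 months | yes | yes, if both follow-ups are modelled |
| WOMAC pain, stiffness | yes | 3, 6 months | yes | yes, if both follow-ups are modelled |
| ICOAP, AQoL-6D, PASE | yes | 6 months | yes | no |
| Global ratings (pain, function) | no | 3, 6 months | no | two follow-ups available |

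K-L grade is available for every participant, because it is an eligibility criterion and the stratum.

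**2. Single follow-up.** Suppose the random effect is a participant intercept with variance τ² and the residual variance is σ². With one row per participant the variance of the outcome is τ² + σ², and only that sum enters the likelihood. In a simulated data set with 65 per arm, the log-likelihood was -156.84 when the participant share was 0%, 25%, 50%, 75% and 95%. The group coefficient was 0.425 from ordinary ANCOVA and 0.425 from the mixed fit. Total variance was 0.669 by ANCOVA and 0.3345 + 0.3345 = 0.669 by the mixed fit. The standard error implied by that total is 0.1435. The mixed-model routine printed 0.1387, a ratio of 0.1387/0.1435 = 0.967, so about 3% too small. That comes from fitting a variance the data cannot identify, and it is a practical reason to name ANCOVA.

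**3. The plan's own sample size.** It supplies the only correlations in the document. Inputs from Sample size calculations: differences of 1.8 (pain) and 6 (function); "between-subject SD of 2.5 for pain and 10.5 units for WOMAC physical function"; correlations 0.29 and 0.51; 90% power; 0.05, taken as two-sided. The formula is n per arm = 2(1.960 + 1.282)² SD²/d².

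- Pain: 2 × 10.51 × 2.5²/1.8² = 40.5, so 41. This matches the stated figure.
- Function: 2 × 10.51 × 10.5²/6² = 64.4, so 65. This matches; 65/0.80 = 81.25, so 82 per arm.
- With the baseline adjustment that the section describes, multiply by 1 - r². Pain: 40.5 × 0.9159 = 37.1, so 38. Function: 64.4 × 0.7399 = 47.6, so 48.

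The stated sizes therefore match the unadjusted formula. That is conservative and separate from this point.

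**4. What can a covariate be worth?** In a linear model, a covariate that has correlation r with the outcome multiplies the standard error by √(1 - r²). At r = 0.29 this is 0.957 (4.3% smaller); at r = 0.51 it is 0.860 (14.0% smaller). These values are for a score with its own baseline and serve only as a scale. The document gives no correlation for K-L grade, or for baseline scores with the global ratings. The formula also does not carry over to logistic or proportional-odds models. There the gain from a prognostic covariate comes as power, and the odds ratio becomes conditional on that covariate.

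**The case against.** The strongest reply is that a journal article condenses. A full covariate list belongs in the analysis plan, and absence of K-L grade from one sentence does not exclude it. The baseline adjustment also stands in the sentence on continuous outcomes; the word similar need not carry it over to the global ratings. And where there is one follow-up, any competent analyst will fit ANCOVA and get the same answer.

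Most of this stands, which is why the point is minor. What remains is that the article does name its adjustment, that it cannot be applied to the global ratings on any reading, and that the stratum is not part of it.

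Two stronger readings are tempting, and the documents support neither.

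- **The primary model estimates an average over 3 and 6 months.** A reader might infer this because no group-by-month term is named. If the 3-month effect were a fraction f of the 6-month effect, a model with one group term would estimate (1 + f)/2 of the target: at an assumed f = 0.5, 6 × 0.75 = 4.5 function units (4.49 in simulation, against 5.99 with the interaction). But the article lists no terms and nowhere pools the two months. It labels 3 months secondary, makes 6 months decisive, and, in the sentence before the model, describes change to each time-point. The shortfall belongs to a model the protocol does not state, and it vanishes at f = 1.
- **The random-effects odds ratio is wrong because it is conditional on the participant.** It will usually lie further from 1 than a between-arm odds ratio: 2.0 becomes 2.23 or 2.92 for assumed intercept SDs of 1 and 2. But it is a legitimate measure, and the protocol promises no other.

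**Conclusion.** The concern holds as a minor point of specification. The global ratings lack the one covariate that the plan names, and K-L grade, which stratifies the randomisation, is not among the stated adjustments for any outcome. Neither biases the treatment comparison; the cost is in precision or power and cannot be sized from the document. For ICOAP, AQoL-6D and PASE the participant effect is not identified, but the group estimate equals that of ANCOVA, so it would be too strong to say that these outcomes cannot be analysed.

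This rests on two assumptions: that the unnamed random effect is a participant intercept, and that the similar models were meant to include the baseline adjustment. If the second is wrong, the global-rating models simply have no stated covariate, and the remedy is the same. The protocol gives no ground to call the primary analysis wrong.

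**What to change.** In Statistical analyses:

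1. Add K-L grade, as a three-level factor, to every between-group model.
2. Adjust the global rating of pain for baseline NRS pain on walking, and the global rating of function for baseline WOMAC function.
3. Specify ANCOVA at 6 months for ICOAP, AQoL-6D and PASE.
4. As clarification only, state that the primary estimate is the 6-month group contrast from a model with a group-by-month term, as Trial design and Outcome measures already imply.

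All the covariates are already collected before randomisation, so there are no new data, visits or participants. K-L grade uses two degrees of freedom (three grades less one). The adjusted odds ratios for the global ratings will be conditional on the covariates and should be labelled so. The wording should be settled before the blind is broken.
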